#### Study goals and objectives

- 1. **Main objectives**

Verify-in patients with psoriasis, living in an endemic area for tuberculosis and vaccinated with BCG, whether MTX significantly changes the frequency of TST and/or IGRA results and concordance between tests and whether positive tests are associated with age, disease duration in years, blood glucose, body mass index (BMI), PASI (psoriasis area and severity index), CRP, erythrocyte sedimentation rate (ESR), TNF-α, IFN-γ, IL-12, IL17 and IL 23 before and after the use of methotrexate for 12 weeks and PASI reduction after treatment.

- 1. **Specifics objectives**

Determining before and after 12 weeks of methotrexate use in psoriasis patients:

- The value of PASI
- The PASI reduction percentage
- Frequency of QuantiFERON negative, positive, indeterminate, and the test agreement.
- The TST results in mm and the test agreement.
- The agreement between TST and QuantiFERON
- The values ​​and means of the inflammatory tests (ESR and CRP)
- The levels of cytokines; TNF-α, IFN-γ, IL-12, IL17, and IL 23.

Verify if after treatment with methotrexate if there is:

- Statistical difference in frequency of positive/negative/ indeterminates TST
- Statistical difference in frequency of positive/negative/indeterminate IGRA
- Statistical difference in frequency in the agreement between TST and IGRA
- Statistical difference in PASI, cytokines and inflammatory tests levels
- Association between positive and negative tests before and after treatment with sex, age, disease duration, weight, blood glucose, BMI, ESR, CRP, PASI, TNF-α, IFN-γ, IL-12, IL17 and IL 23, absolute PASI and Percentage reduction of PASI before and after treatment.
  1. **Secondary objectives**
- Characterize the clinic and demographic characteristics of the sample following the variables sex, age, weight, BMI, disease duration in years, diabetes, associated psoriasis forms: geographical tongue, palmoplantar psoriasis, psoriasis of the scalp, inverted psoriasis, nail psoriasis, place of residence (urban or rural), contact with cattle, alcohol intake, smoking, prior contact with a tuberculosis carrier, chest X-ray abnormality suggestive of TBLI,

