3.2 Sampling type and sample size definition

The sample will be systematic random.

It will be included sequentially patients over 18 years of age with moderate to severe plaque psoriasis with the indication of methotrexate referred by dermatologists to initiate the follow-up in the outpatient clinics of the Hospital of the Federal University of Pernambuco who meet the eligibility criteria and sign the consent form.

The sample size calculation was performed considering the effect of MTX on PASI. The calculation used the formula for comparing paired differences.

To achieve a power of 80 % and a level of significance of 5 % (two-sided) for detecting an effect size of 0,65 between pair was necessary 22 pairs.

For the other variables, the objective was to verify if this effect produced on the PASI would be sufficient to produce a change in them.

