#### Data analysis plan

The IBM Statistical Package version 23.0 (IBM corp., Armonk, NY) will be used for the statistical calculations.

- Data will be analyzed descriptively through statistical measures: mean ± standard deviation or median and percentiles for numerical variables and absolute and percentage frequencies for categorical variables.
- It will be verified whether there is a significant change in the results of TST and/or IGRA tests, with 2 or 3 categories, classified according to the variables descriptions by the McNemar test. A P < 0,05 will be considered significant.
- It will be verified whether the difference in the comparison of test results is significant before and/ or after treatment by the McNemar test. A P < 0,05 will be considered significant.
- The agreement between each and between the IGRA and the TST before and after treatment, with two or three categories, will be verified by the Cohen’s kappa.
- For numeric continuous variables, the normality will be tested using the Shapiro-Wilk test. To compare the mean of paired continuous variables will be used the Student's t-test for paired variables for variables with a normal distribution, and the Wilcoxon test for variables with a non-normal distribution.
- To compare the TST and IGRA results with the means of numerical continuous variables will be used the Student's t-test for variables with a normal distribution, and the Mann-Whitney test for variables with a non-normal distribution.
- Will be verified the association between the sustainers or non-sustainers status with the categorized variables by the Fisher Exact test. The variables presenting p < 0.05 will be considered a positive association. The variables will be sex, age categorized, duration of illness categorized, alcohol consumption, smoking, presence of other forms of psoriasis associated, blood glucose (normal, diabetic).
- The association between the sustainers or non-sustainers status with the medians/medians of the continuous variables will be verified by t-Student test or Mann-Whitney test, The variables will be the age in years, disease duration in years, BMI, blood glucose in mg/dl, serum levels of INF-γ, TNF-α, interleukin-12, interleukin-17, interleukin-23, ESR, CPR. The association with ESR, CPR, and cytokines will be verified before and after treatment.
- The variables presenting p < 0.05 will be considered a positive association.

.

1. ***Budget****

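### The main objective asks whether MTX changes TST-IGRA agreement, but the analysis plan clearly specifies only a kappa at each visit, with no test or interval for the change

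*Protocol*

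**What the plan says.** The main objective (protocol section 2) asks "whether MTX significantly changes the frequency of TST and/or IGRA results and concordance between tests". The list of things to verify after treatment includes "Statistical difference in frequency in the agreement between TST and IGRA". Describing TST-QuantiFERON agreement before and after is a separate item under the specific objectives, so the protocol asks for both a description and a test of change.

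Section 5 (Data analysis plan) has three relevant bullets:

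- A McNemar test, at P < 0.05, of "whether there is a significant change in the results of TST and/or IGRA tests, with 2 or 3 categories".
- A second check, also at P < 0.05, of "whether the difference in the comparison of test results is significant before and/ or after treatment by the McNemar test".
- For agreement: "The agreement between each and between the IGRA and the TST before and after treatment, with two or three categories, will be verified", by Cohen's kappa. This bullet has no comparison of the two kappas, no interval and no significance rule.

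Section 4.2 defines two- and three-category codings for each test. In the two-category coding, TST is positive from 5 mm and an indeterminate QuantiFERON counts as positive. No variable for agreement status is defined. Section 3.2 sizes the study at 22 pairs on the effect of MTX on PASI.

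**The concern.** The objective is inferential: does the frequency of agreement change under MTX? Section 5 supplies two separate descriptions, one kappa per visit. Comparing them by eye in 22 patients does not test change. A p-value attached to a single kappa would not help, because it tests kappa = 0 at that visit.

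The choice of statistic adds a second problem. The other half of the same objective is whether MTX shifts the frequency of positive results, and kappa moves with that frequency even when the tests agree equally often. So a real loss of agreement could go untested, or a shift in positivity could be reported as a loss or gain of concordance.

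**Working it through.** **Inputs.** From the protocol: 22 pairs, effect size 0.65, two-sided 5%, power 80% (section 3.2), and the two-category codings (section 4.2). The protocol gives no expected positivity, agreement or change, so every table below is an assumption. Tables read: both positive / TST only / IGRA only / both negative.

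**1. The plan's own figure.** Normal approximation: ((1.960 + 0.842)/0.65)² = 18.6, so 19 pairs. The exact paired t calculation gives 21 pairs (power 80.9%), and 22 pairs give 82.8%. Allowing for a Wilcoxon test, 21/0.955 = 22.0. The stated 22 is reproduced, for PASI. No figure is given for concordance.

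**2. Does the second McNemar bullet test agreement?** Take it as TST versus IGRA at one visit. With b and c the two discordant counts, exact p = min(1, 2·P[X ≤ min(b, c)]), X ~ Bin(b + c, ½). It uses only the balance of the discordant cells.

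| Table | Agreement | Kappa | McNemar p |
|---|---|---|---|
| 9/2/2/9 | 18/22 = 82% | 0.64 | 1 |
| 6/5/5/6 | 12/22 = 55% | 0.09 | 1 |
| 5/6/6/5 | 10/22 = 45% | -0.09 | 1 |
| 2/9/9/2 | 4/22 = 18% | -0.64 | 1 |

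Agreement runs from 82% to 18% and the test does not register it. It compares positivity rates.

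**3. Does kappa track the frequency of agreement?** Kappa = (po - pe)/(1 - pe). Hold po at 18/22 = 0.818:

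- 8/2/2/10 (10 positive on each test): pe = (10² + 12²)/22² = 0.504, kappa = 0.314/0.496 = 0.63.
- 2/2/2/16 (4 positive): pe = (4² + 18²)/22² = 0.702, kappa = 0.116/0.298 = 0.39.
- 16/2/2/2 (18 positive): pe = (18² + 4²)/22² = 0.702, kappa = 0.39.
- 9/2/2/9 (11 positive): pe = (11² + 11²)/22² = 0.500, kappa = 0.318/0.500 = 0.64.

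Going from the first table to the second, positives fall and kappa falls. Going from the third to the fourth, positives also fall, yet kappa rises. Agreement is 18/22 throughout.

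**4. Precision of one kappa at n = 22.** Large-sample 95% limits are 0.31 to 0.96 for kappa 0.64 (9/2/2/9), and -0.10 to 0.88 for kappa 0.39 (2/2/2/16). These apply to each kappa alone. The paired difference has its own standard error, which depends on the joint before-after data.

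**5. What a paired test of agreement status can do.** Suppose agreement falls from 18/22 to 10/22 (9/2/2/9 to 5/6/6/5). The net loss is 8, and up to 4 patients may gain agreement. Exact McNemar p by lost/gained: 8/0, 0.008; 9/1, 0.021; 10/2, 0.039; 11/3, 0.057; 12/4, 0.077. The visit-wise TST-versus-IGRA test gives p = 1 both times, whatever the pairing.

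For p < 0.05 at least 6 patients must change status, and with exactly 6 all must go the same way (6/0: 2 × 0.5⁶ = 0.031; 5/0: 0.0625). Exact power at 22 pairs sums, over the possible numbers of changers, the probability of a significant split: 24% if 25% lose and 5% gain agreement, 38% for 30% versus 5%, 65% for 40% versus 5%, and 75% for 45% versus 5%.

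**The case against.** The strongest reply concerns the second McNemar bullet. Section 2 lists three before-after differences for the TB tests (TST, IGRA, and their agreement), and section 5 has two McNemar bullets. By position, the second could be meant for agreement. A reader might therefore infer from this point that the plan contains no test of the change at all. The text does not support so flat a statement, because the bullet is ambiguous. It does not settle the matter either: its wording fits TST versus IGRA at each visit better, and the agree/disagree variable that the other reading needs is defined nowhere. If that reading was intended, the sentence still has to be written.

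A reader might also infer that kappa must fall if MTX lowers positivity. That is not supported. The protocol gives no baseline positivity, and in a BCG-vaccinated sample from an endemic area, with TST positive from 5 mm, a high starting level cannot be excluded. In that case kappa could rise.

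The plan also offers partial protection, since it reports frequencies and tests the shift in each test's positives. In the move from 10 to 4 positives, that test gives p = 0.031 if six patients revert and none convert, which would help explain a lower kappa. With seven reverting and one converting, p = 0.070 and the signal is weaker. Neither result says whether agreement changed.

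Finally, kappa is conventional and an interval for it could be left to a SAP, which is not shown. That is fair for the interval. It does not cover a protocol that fixes a method which leaves its own objective unanswered.

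**Conclusion.** The mismatch stands. A stated part of the main objective has no clearly specified test, and the statistic that is specified can move in either direction with agreement unchanged (0.63 to 0.39, or 0.39 to 0.64, at 18/22). The second McNemar bullet is ambiguous; on its natural reading it tests neither agreement nor its change.

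The arithmetic is exact for the tables shown, but the tables are assumed. They show what can happen, not what is likely. In particular, p = 0.008 for a fall from 18 to 10 is the most favourable pairing; the least favourable gives 0.077. A reader should not conclude that the paired test would reliably detect such changes, because the sample was sized on PASI and power for agreement is modest.

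This should be fixed. Data collection is unaffected and the other parts of the main objective keep their analyses.

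**What to change.** In section 5:

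- Code each patient at each visit as TST-IGRA agree or disagree. Use the two-category coding of section 4.2 for the main analysis, stating that it counts an indeterminate QuantiFERON as positive. Use the three-category coding as a supplementary analysis, so that the planned two-or-three-category scope is kept.
- Test the before-after change in that status with the exact McNemar test, and report the paired difference in percent agreement with a 95% CI.
- Keep kappa descriptive. If a change in kappa is reported, give a bootstrap CI that resamples patients with both visits kept together.
- Reword the second McNemar bullet to say what it compares. If it is TST versus IGRA at each visit, state that it compares positivity rates and is not a test of agreement.
- State that the 22 pairs were sized on PASI, that power for agreement is limited, and that a non-significant result will not be read as preserved concordance.

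The cost is a few sentences and a little analysis work on data already planned. The small downside is a test that may often be non-significant, which is why the interval should carry the conclusion.

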It has been suggested that the interferon-γ (IGRA) release assay should replace the use of TST in the TBLI screening because it has greater sensitivity and specificity (BELO et al., 2014). However, the studies comparing patients with psoriasis and normal controls observed a lower concordance of TST(LAFFITTE et al, 2009; LIMA, 2013). It was then questioned whether the reason was the interference of the disease itself (LAFFITTE et al., 2009; DE ANDRADE LIMA et al., 2011), immunosuppression (BARTALEZZI et al, 2009; RAMOS et al., 2013, CONSTANTINO et al., 2013, HELWIG et al, 2012; CHIU, HSUEH, TSAI, 2011) or epidemiological factors such as age (TAVAST et al., 2012), contact with cattle ((RAMOS *et* *al*, 2013; LAFFITTE *et* *al*, 2009)) or vaccination with the Bacilli of Calmette-Guérin (SAUZULLO *et al*., 2013; LAFFITTE *et* *al*, 2009).

The test possibly affected by immunosuppression is also controversial. Some studies have found that immunosuppression affects the results of IGRA (BERTALEZZI et al, 2009, RAMOS et al, 2013, CONSTANTINO et al, 2013, HELWIG et al, 2012) while others the TS T (TAVAST et al., 2012) and there are still those that did not find an influence on both tests (MARTYN-SIMMONS et al., 2012; LATORRE et al., 2014). As many patients with psoriasis are screened for TBLI using an immunosuppressant, more often methotrexate (MTX) (DAUDÉN et al., 2016), it becomes important to elucidate whether immunosuppression interferes with TBLI screening tests.

There are several reasons why the issue has not been elucidated. Most studies evaluating the effect of immunosuppression are retrospective and present factors that may influence test results (CONSTANTINO et al 2013, RAMOS et al, 2013) as individuals with varied diseases, heterogeneous BCG vaccination status and geographic region of origin. (BARTALEZZI et al, 2009, TAVAST et al, 2012, RAMOS et al, 2013).

The search for an association between the results of screening tests with factors that could infer the impact of immunosuppression such as the degree of clinical control, variation in the inflammatory and immunological markers received little attention so far. Sauzullo et al. (2013) described in-vitro a reduction in the levels of interferon-gamma (IFN-γ) specific for TB inversely proportional to levels of a tumor necrosis factor alpha blocking drug.

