4.2 Variables definition

| Variable | Definition | Categorization |
| --- | --- | --- |
| ***TB screening*** | |  |
| **Quantiferon TB- gold first categorization** | Tests classified as positive by the manufacturer | 1. Positive |
|  | Tests classified as positive by the manufacturer | 1. Indeterminate |
|  | Tests classified as positive by the manufacturer | 1. Negative |
| **QuantiFERON TB-gold second categorization** | Tests classified as positive or undetermined | 1. Positive |
|  | Tests classified as negative | 1. Negative |
| **TST first categorization** | <5 mm | 1. Negative |
|  | 5 mm ≤ TST < 10 mm | 1. Indeterminate |
|  | ≥ 10 mm | 1. Positive |
| **TST second categorization** | <5 mm | 1. Negative |
|  | ≥ 5 mm | 1. Positive |

| *Cytokines* | |  |
| --- | --- | --- |
| **TNF-α** | in pg/ml | Average |
| **IFN-γ** | in pg/ml | Average |
| **IL -12** | in pg/ml | Average |
| **IL- 17** | in pg/ml | Average |
| **IL-23** | in pg/ml | Average |
| ***Inflammatory markers*** | |  |
| **CRP** | in mg/l | 1. ≤ 1 2. > 1 |
|  |  | Average |
| **ESR** | in mm/h | 1. ≤10 2. >10 |
|  |  | Average |
| ***Clinic*** |  |  |
| **PASI absolute** | psoriasis severity index calculated as described in methods | Mean/median |
| **PASI reduction** | Percentage reduction of PASI after the use of methotrexate | 1. <50% 2. 51-74% 3. > 75 %   Média/mediana |

| Variable | Definition | Method | Categorization |
| --- | --- | --- | --- |
| Sex | Biological gender of the patient | Interview | 1. Male 2. Female |
| Age | The time between the date of birth and study interview day, in full years | Identification document | 1. *18 ≥ x* < *30* 2. *30 ≥ x < 60* 3. *≥ 60*   Average |
| Disease duration | Estimated time between the age of onset of illness and the age at study interview day in full years | Interview | 1. < 2 year 2. 2 *≥ x <* 10 years 3. *≥ 10*  years   Average |
| alcohol intake | Have consumed more than one dose per day if the patient is a woman or 2 doses if is a man in the last 30 days. | Interview | 1. Yes 2. No |
| Smoking | I have smoked for more than one day in the last 30 days. | Interview | 1. Yes 2. No |
| Contact with Tb carrier | Characterized by a family history of TB (parents, uncles, grandparents, partners, children or own patient), know someone with TB as a neighbor, friends, co-workers or works in a high-risk TB environment | standardized questionnaire | 1. Yes 2. No |

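### Disease duration is compared between test-positive and test-negative patients without age, so an age effect on the tests can appear as an association with duration

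*Protocol*

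**What the plan says.** The main objective (Protocol, section 2) asks "whether positive tests are associated with age, disease duration in years, blood glucose, body mass index (BMI), PASI", and continues with inflammatory markers, cytokines and PASI reduction. Age and disease duration are thus two separate candidates in one list of 13 variables.

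The data analysis plan (section 5) gives the method: "To compare the TST and IGRA results with the means of numerical continuous variables will be used the" t-test where the distribution is normal, with Mann-Whitney otherwise. Its decision rule is: "The variables presenting p < 0.05 will be considered a positive association". The section names no regression, stratification or other adjustment for any analysis.

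Section 4.2 defines disease duration as "Estimated time between the age of onset of illness and the age at study interview day in full years". The inclusion criteria (section 3.3) admit patients over 18 with no upper limit. The rationale (section 1), discussing why the two tests agree less well in psoriasis, lists interference by the disease, immunosuppression, and "epidemiological factors such as age", among other factors. The study responds by keeping BCG profile and region of origin uniform. It does not do the same for age.

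**The concern.** Duration equals age at interview minus age at onset, so it cannot exceed age and will usually rise with it. How strongly depends on how onset age varies with current age, which the protocol does not give. If older patients are more often test-positive for reasons unrelated to psoriasis, positives will also tend to have longer disease. A two-group test on duration alone cannot distinguish that from an association of duration in its own right.

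What is at stake is the association part of the main objective. Under the stated rule, duration could be reported as associated with positive tests when the data show only that positives were older.

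**Working it through.** **The plan's own figure.** Section 3.2 gives 22 pairs for 80% power, two-sided 5%, effect size 0.65 on PASI. The normal approximation gives ((1.96 + 0.84)/0.65)² = 18.6, so 19. The exact paired t calculation gives 21 (power 80.9%; 22 pairs give 82.8%), and 21/0.955 = 22.0 if the Wilcoxon test is allowed for. The 22 reproduces. It was set for PASI change, not for the association analyses, and serves here only as the number of patients.

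**Inputs from the protocol.** 22 patients; two-sided 5%; unadjusted t or Mann-Whitney test; duration defined from age at interview.

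**Assumed inputs (the protocol gives none of these).** 7 test-positive and 15 test-negative patients; positives older by d = 0.5, 0.8 or 1.2 SD; correlation between age and duration r = 0.4 or 0.6; no effect of duration itself.

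**Formula.** With no effect of its own, duration still differs between the groups by r × d SD. The t-test has 20 degrees of freedom and noncentrality r × d × √(7 × 15/22) = r × d × 2.185.

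| d | r | r × d | Noncentrality | Unadjusted, calculated | Unadjusted, simulated | Age-adjusted, simulated |
|---|---|---|---|---|---|---|
| 0.5 | 0.4 | 0.20 | 0.44 | 7.0% | 7.1% | 5.2% |
| 0.5 | 0.6 | 0.30 | 0.66 | 9.6% | 9.7% | 5.8% |
| 0.8 | 0.4 | 0.32 | 0.70 | 10.2% | 10.2% | 5.7% |
| 0.8 | 0.6 | 0.48 | 1.05 | 17.0% | 16.8% | 5.8% |
| 1.2 | 0.4 | 0.48 | 1.05 | 17.0% | 16.6% | 5.5% |
| 1.2 | 0.6 | 0.72 | 1.57 | 32.2% | 32.5% | 5.3% |

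The last two columns give the share of simulated studies with p < 0.05. With d = 0 the rate is 5%.

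**Mann-Whitney.** In a separate run of 8,000 studies per setting, this alternative gave 9.4% and 15.2% at d = 0.8 (r = 0.4 and 0.6), and 15.9% and 29.3% at d = 1.2. Switching to the rank test does not protect against the problem.

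**A different model.** Here age acts on the odds of a positive test, about 40% of 22 patients are positive (assumed), and there are 6,000 studies per setting. Odds ratios per SD of age are 1.5 / 2 / 3.

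| r | Unadjusted rejection |
|---|---|
| 0 | about 5% throughout |
| 0.3 | 6.0% / 7.4% / 8.4% |
| 0.5 | 6.4% / 11.2% / 16.6% |
| 0.7 | 9.1% / 15.6% / 28.5% |

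With age as a covariate the rate is 4.5% to 5.8% in these settings.

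**Cost of adjusting.** For a marker unrelated to age, adding age multiplies the variance of the group difference by about 1 + p(1 − p)d², with p = 7/22 and p(1 − p) = 0.217. At d = 0.8 this is 1.14, a standard error about 7% larger. At d = 1.2 it is 1.31, about 15% larger.

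**The case against.** A reader might infer that the plan declares an age effect to be a disease effect. It does not: its wording is association throughout, without causal claims. Age is itself tested against the results, so an imbalance could be seen. That stands, but seeing an imbalance does not separate age from duration, and with about 22 patients a real imbalance may go undetected.

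A reader might also take the rationale as setting age against disease as rival causes of a positive test. The sentence concerns reduced concordance between TST and IGRA and lists several other factors. It shows that the protocol regards age as a possible influence on results, and no more.

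It is tempting to extend the point to PASI, CRP, ESR and the cytokines. Nothing in the protocol links these to age, and a marker unrelated to age suffers no inflation. The protocol's disease hypothesis rests on immune activation and on clinical and inflammatory activity, so duration is a secondary expression of it.

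The objection can also be made that these rejections are not errors at all, because mean duration really does differ between the groups and the marginal association is what was asked for. That is correct for the marginal question. The rates above are error rates only for the question whether duration matters beyond age, which the planned test cannot answer.

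Finally, adjustment has a limit: with age fixed, duration and age at onset carry the same information, so the adjusted result cannot tell those two apart.

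**Conclusion.** The point holds for disease duration. The plan fixes an unadjusted comparison for a variable built from age, in a sample with no upper age limit, and the main objective lists both. An age effect on the tests can then pass as a positive association with duration, in about 7% to 33% of studies under the assumed settings, against about 5% to 6% with age in the model. The split, age gap and correlation are all assumptions. The lower end is close to nominal, and there is no inflation if age does not differ between the groups or is uncorrelated with duration.

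The documents do not support saying that a false duration finding is the likely outcome: even in the worst setting about two thirds of studies would show none. Nor do they support making age-adjusted models the main result for every marker. This is an inexpensive improvement to the analysis wording and does not invalidate the planned comparisons.

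**What to change.** In the data analysis plan, add for disease duration a linear model of duration in years (or its rank, if non-normal) on test status plus age in years. Report the age-adjusted difference with its 95% confidence interval beside the planned unadjusted result. Describe duration as associated independently of age only if the adjusted result supports it.

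For the other continuous markers, keep the planned t or Mann-Whitney tests, label them unadjusted and exploratory, and give the age-adjusted estimate as a sensitivity analysis.

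Age is already recorded for every patient, so no new data are needed. The cost is one degree of freedom in about 22 patients and a somewhat wider interval, with a standard error up to about 15% larger if positives are much older and the marker is unrelated to age. With so few patients, one covariate is about as many as is realistic.

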- Verify the association between the sustainer status with sex, age categorized, disease duration, weight, BMI, alcohol consumption, smoking, presence of other forms of psoriasis associated, blood glucose (normal, diabetic), serum levels of INF-γ, TNF-α, interleukin-12, interleukin-17, interleukin-23, ESR, CPR. The association with ESR, CPR, and cytokines will be verified before and after treatment. The variables presenting p < 0.05 will be considered a positive association.

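### Age and disease duration are each tested twice against sustainer status with no rule for which test decides, and the class limits used in the weaker test are misprinted

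*Protocol*

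**What the plan says.** The protocol's Data analysis plan has two bullets on sustainer status.

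- The first uses Fisher's test: "Will be verified the association between the sustainers or non-sustainers status with the categorized variables by the Fisher Exact test". Its list begins "The variables will be sex, age categorized, duration of illness categorized, alcohol consumption, smoking".
- The second uses the t-test or Mann-Whitney. Its list begins "The variables will be the age in years, disease duration in years, BMI, blood glucose in mg/dl".

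Age and disease duration are in both lists. The same threshold, p < 0.05, makes any of these results a positive association. No sentence ranks the two versions.

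The matching item under Secondary objectives asks for the association of "the sustainer status with sex, age categorized, disease duration, weight, BMI" and further variables. Age is categorised there; disease duration has no stated form.

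Section 4.2 defines the classes. Age is printed as 18 ≥ x < 30, 30 ≥ x < 60, and ≥ 60. Disease duration is printed as < 2, 2 ≥ x < 10, and ≥ 10 years.

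Section 3.2 bases the sample size on another outcome: "The sample size calculation was performed considering the effect of MTX on PASI". It concludes "for detecting an effect size of 0,65 between pair was necessary 22 pairs".

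**The concern.** Two tests of one question, each with its own claim to significance and no rule between them, leave the conclusion open until the data are seen. A reader of the results could be shown either one.

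The two versions are also unequal. Fisher's test on a 3×2 table ignores the order of the classes and all differences within a class. In a sample of about 22 that loss is large, and for age it falls on the version that the objective names.

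The class limits matter because nothing else in the protocol tells the analyst how to form the groups for the Fisher test.

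**Working it through.** **Sample size.** Section 3.2 gives effect size 0.65, 80% power and two-sided 5%.
- Normal formula: (1.960 + 0.842)² / 0.65² = 7.85 / 0.4225 = 18.6, so 19 pairs.
- Paired t-test with the noncentral t: 21 pairs (power 0.809; 0.828 at 22).
- Allowing for the Wilcoxon test: 21 × π/3 = 21.99, so 22 pairs.

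The stated 22 is reproduced and is used below. It was not derived for sustainer status.

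**Age, class test against years test.** The protocol gives no age distribution and no expected number of sustainers, so these are assumptions: 11 sustainers and 11 non-sustainers, age mean 45, SD 14, and classes as evidently intended (under 30, 30-59, 60 and over). There were 8,000 simulated trials per effect size, comparing the exact 3×2 Fisher test with the pooled t-test at two-sided 0.05.

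| True difference | Fisher, 3 classes | t-test, years | Either positive |
| --- | --- | --- | --- |
| 0 | 3.2% | 5.1% | 7.2% |
| 0.8 SD | 19.2% | 43.4% | 45.8% |
| 1.0 SD (14 years) | 30.3% | 62.0% | 63.7% |

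What the class test adds to the years test:
- Power at 1 SD: 63.7 − 62.0 = 1.7 points. At 0.8 SD: 45.8 − 43.4 = 2.4 points.
- False positives with no effect: 7.2 − 5.1 = 2.1 points.

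Disagreement at 1 SD: significant by t-test only, 63.7 − 30.3 = 33.4%; by Fisher only, 63.7 − 62.0 = 1.7%; together about 35% of trials.

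**Other assumptions.** A second simulation used 10,000 runs per cell, three age distributions (mean/SD 45/15, 50/13, 40/15) and log-normal duration with median 8 or 12 years. Power at 1 SD:

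| Split | Age: Fisher | Age: t-test |
| --- | --- | --- |
| 11:11 | 0.27-0.32 | 0.60-0.61 |
| 14:8 | 0.25-0.30 | 0.57 |
| 16:6 | 0.22-0.27 | 0.49-0.51 |

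For duration, Fisher against Mann-Whitney gave 0.29-0.32 against 0.58 (11:11) and 0.30-0.33 against 0.47-0.48 (16:6).

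The gap narrows as the effect grows. The ratio of Fisher to t-test power for age is 0.38-0.55 at 0.8-1.0 SD and 0.64-0.72 at 1.5 SD. With no effect, at least one of a variable's two tests is positive in about 5-8% of trials.

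**Class limits read literally.**
- 18 ≥ x < 30 reduces to x ≤ 18. Section 3.3 admits patients over 18, so this class is essentially empty.
- 30 ≥ x < 60 reduces to x ≤ 30. Ages 19-30 land here, and ages 31-59 land nowhere.
- 2 ≥ x < 10 reduces to x ≤ 2. Durations of 3-9 full years land nowhere, and durations under 2 years satisfy two classes.

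Changing the first ≥ to ≤ in these three classes closes every gap and overlap.

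**The case against.** **The plan loses no power.** This is correct. A reader might infer from 30% against 62% that the sustainer analysis has half the power it should. The years test is already planned, so accepting either result gives 63.7% against 62.0% for years alone. The loss belongs to the class test taken by itself.

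**The disagreement mostly restates the power gap.** Also fair. Of the 35%, 33.4 points are a significant t-test beside a non-significant Fisher test. Those are not opposite conclusions, but the protocol still does not say which is the result.

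**The false-positive cost is small within a long list.** Counting other psoriasis forms as one item, there are 7 Fisher tests. There are 4 + 7 × 2 = 18 continuous ones (four variables tested once, seven markers before and after treatment). The repair removes 2 of about 25 unadjusted tests. Testing is doubled for age and duration, not for the whole analysis.

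**The objective does not name the class form for both variables.** True; it does so for age only.

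**The limits are an obvious misprint.** Agreed. A reader might infer that most patients would go unclassified. The documents give no age or duration distribution to support that. Under assumed distributions the literal share in no class is 49-71% for age (means 35-60) but 29-45% for duration (medians 3-15 years). An analyst would in any case see the intended limits.

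**The t-test is not always better for duration.** On skewed duration it can do worse than Fisher (0.15-0.18 against 0.30-0.33 at 16:6, 1 SD). The advantage holds for Mann-Whitney, which the plan already assigns to non-normal variables.

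**Precedence could be left to a statistical analysis plan.** One may exist. But the protocol itself fixes both tests and the threshold for each, so the conflict is in its own text.

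**Conclusion.** Two narrow points stand.

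1. **One test per variable would be better at almost no cost.** Under the assumed 11:11 split and age SD of 14, dropping the class test brings the false-positive rate for age from about 7% back to about 5% and gives up about 2 points of power. Other assumed splits and age distributions show the same pattern for age. For duration, the class test is likewise the weaker one when compared with Mann-Whitney.
2. **The class limits are wrong as written.** The intent is clear, but section 4.2 is the only definition of groups that enter a planned test.

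The analysis is a secondary objective and the sample was not sized for it, so the effect on the trial is small. The evidence does not support a claim that the plan as a whole is underpowered by this choice, or that patients would actually be lost from the classes.

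**What to change.** - **Data analysis plan:** take the class versions of age and disease duration out of the Fisher list. State that inference for both uses years, with Mann-Whitney where the distribution is not normal, as the plan already provides.
- **Secondary objectives:** name both variables in years. Replace the form of age rather than deleting the entry, which would drop age from the objective.
- **Section 4.2:** change the first ≥ to ≤ in the two lower age classes and the middle duration class, so that every patient falls in exactly one class. Keep the classes for description only.

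Blood glucose also appears in both lists, as normal/diabetic and in mg/dl. Diabetes is defined partly by medication, so it is not simply a cut of the glucose value. One sentence saying which form decides would settle it.

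The cost is two items removed, two phrases changed and three signs corrected. No data collection changes.
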